### Relevant concomitant care permitted or prohibited during the trial {11d}

Standard bowel prep, IV access, and rescue medications for hypotension/nausea are permitted, while sleep aids (7 days pre-op), additional sedatives/analgesics (opioids, benzodiazepines) during procedure/PACU stay, and elective surgeries within 72 h post-procedure are prohibited. All concomitant treatments will be documented in CRFs.

### Provisions for post-trial care {30}

Once upon gastroscope removal, sedation will be stopped. Patients with spontaneous respiration ability will be transferred to the PACU. Symptomatic supportive treatment according to clinical practice will be given, recording on CRFs and reporting to IRB.

### Outcomes and definitions {12}

Primary outcome is the hypoxemia incidence, defined as SpO_2_ < 90% for > 10 consecutive seconds during the procedure [18]. Timing begins at first SpO_2_ reading < 90% and continues until resolution.

Secondary outcomes are as follows:Severe hypoxemia incidence, defined as SpO₂ ≤ 75% for any duration or SpO₂ ≤ 90% for ≥ 60 consecutive seconds or longer during the procedure [17].Hypoxemia duration, defined as total cumulative time (seconds, mean [SD]/median [IQR]) with SpO₂ < 90% during procedure.Emergency airway intervention, defined as requiring jaw thrust maneuver, mask-assisted ventilation with procedure interruption, tracheal intubation during procedure and in PACU.Hypotension incidence defined as MAP decrease ≥ 20% compared with baseline (average of 3 pre-procedure readings) during procedure and in PACU.Involuntary body movements are defined as any limb/trunk movements requiring physical restraint or procedure interruption during the procedure.Total propofol dose defined as cumulative amount (mg, mean [SD]/median [IQR]) administered during procedure.Length of procedure (minutes, mean [SD]/median [IQR]) defined as the time quantum from gastroscope insertion to complete withdrawal.Recovery time (minutes, mean [SD]/median [IQR]) defined as the time quantum from scope removal to achieving MOAA/S score of 5 or responsive to normal voice.Clinician satisfaction measured via 10-cm VAS immediately post-procedure (0 = extremely dissatisfied, 10 = completely satisfied) after the procedure.AEs will be documented and assessed continuously during the procedure and in the PACU. Occurrence counts and severity (where applicable) will be documented in the CRFs as follows:Cough: Defined as ≥2 consecutive coughs during the procedure or in the PACU; assessed by direct observation and recorded as presence/absence.Hiccups: Defined as ≥2 episodes within 1 minute; recorded as presence/absence during the procedure or in the PACU.Nausea/vomiting: Graded on a 3-point severity scale (1=mild/nausea only, 2=moderate/transient vomiting, 3=severe/prolonged vomiting) and assessed both during the procedure and in the PACU.Reflux/aspiration: Defined as visible gastric content in the oropharynx or airway; recorded as presence/absence during the procedure.Laryngospasm: Defined as complete airway obstruction with no airflow despite respiratory effort; assessed by auscultation and waveform capnography, and recorded as presence/absence during the procedure.

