## Introduction

### Background and rationale {6a}

Gastric cancer is among the most prevalent and lethal malignancies globally [1]. Early detection through screening can improve five-year survival rates to approximately 70%, while advanced-stage disease carries a significantly poorer prognosis of about 20% survival [2, 3]. Gastroscopy serves as the gold standard for both screening and early diagnosis of gastric neoplasms. Propofol sedation, while improving patient comfort, frequently induces hypoxemia and hypotension [4], complications exacerbated in patients with moderate-to-high risk OSA (STOP-Bang score ≥ 3) [5, 6].

The pathophysiology of sedation-associated hypoxemia in these patients involves multiple factors: anatomical airway narrowing, increased thoracic negative pressure, gastroesophageal reflux, chronic pharyngitis, and excessive sedative dosing. OSA has been independently associated with hypoxemia during endoscopic procedures [7], and its prevalence in the general population ranges from 2 to 26% [8]. These findings underscore the critical importance of optimal airway management and judicious sedative selection in this vulnerable population.

The ideal sedative adjunct should simultaneously reduce propofol requirements while minimizing adverse effects on oxygenation and hemodynamics, while still maintaining excellent procedural conditions. Current alternatives present significant limitations: midazolam and opioids exacerbate respiratory and cardiovascular depression [9]; ketamine may induce psychotomimetic effects [10]; dexmedetomidine frequently causes prolonged hypotension and bradycardia [11, 12]; and intravenous lidocaine carries toxicity risks [13].

Esketamine, the S-enantiomer of ketamine, offers several pharmacological advantages as an NMDA receptor antagonist. It provides synergistic sedation and analgesia while exhibiting minimal respiratory depression [14, 15]. Clinical studies demonstrate its propofol-sparing effects and excellent safety profile during urological procedures in elderly patients [16]. At the studied dose (0.25 mg/kg), its potential side effects—including transient hypertension, tachycardia, and emergence phenomena—are typically mild and self-limited [17]. However, evidence regarding esketamine’s efficacy in preventing hypoxemia during gastroscopy in moderate-to-high risk OSA patients remains limited.

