### Intervention description {11a}

The anesthesia assessment should be completed a few days before the gastroscopy at Anesthesiology Clinic according to ASA guidelines. Once admitted to the gastroscopy room, intravenous (IV) access will be established, standardized monitoring will be continuously performed, including electrocardiogram (ECG), noninvasive blood pressure (NBP), SpO_2_, respiratory rate (RR), and waveform capnography. Then, placed in a left lateral position, investigators will deliver preoxygenation via facemask at 6 L/min.

Sedation protocol: An initial bolus of propofol (1.0–2.0 mg/kg for patients > 70 years; 1.5–2.5 mg/kg for patients < 70 years) injected. Then, esketamine 0.25 mg/kg is injected for the patients in Group E, while equal-volume saline solution is administered for Group C. Additional propofol (10–50 mg) boluses could be titrated until the palpebral reflex disappears or Modified Observer’s Assessment of Alertness/Sedation (MOAA/S) score of 2. During the procedure, additional propofol (10–50 mg) could be administered again for maintaining a MOAA/S score of 2 or addressing cough (≥ 2 consecutive coughs), grimaces (visible facial muscle contraction), involuntary body movements (limb/trunk movements requiring restraint), and hemodynamic instability (mean arterial pressure [MAP] increase ≥ 20 mmHg or heart rate [HR] increase ≥ 20 beat/min).

Emergency Airway Management: If the SpO_2_ dropped below 90% during the procedure, the airway management protocol in Fig. 2 will be implemented, redesigned according to the clinical practice and another completed trial [17]. If certain emergency situations occur, such as laryngeal spasm, an additional propofol (20–50 mg), methylprednisolone (40–80 mg, increasing the oxygen flow, gastroscope withdrawal, and positive pressure ventilation via the face mask, even rocuronium bromide 0.6 mg/kg and tracheal intubation if needed. No modification of randomized intervention (esketamine/saline); propofol dosing could be adjusted per clinical need (MOAA/S score).

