Notably, our secondary outcomes will provide important insights into esketamine’s multidimensional effects, including the following: propofol-sparing potential and hemodynamic stability [16], reduction in involuntary movements through analgesic properties, clinician satisfaction and procedural conditions, and recovery characteristics. These assessments may help explain the mechanistic basis for any observed hypoxemia reduction while evaluating the overall clinical utility of this adjunctive approach. Our preliminary data in urologic procedures [16] and analogous studies in other contexts [26] support the biological plausibility of our hypothesis.

Potential limitations include the single-center design and focus on gastroscopy, which may affect generalizability. However, the standardized protocol and objective endpoints strengthen internal validity. Furthermore, our stratified randomization and rigorous monitoring protocols minimize confounding and ensure data quality.

This trial will provide high-quality evidence regarding esketamine’s role in improving sedation safety for OSA patients. Positive results could establish a new standard of care for this high-risk population, while negative findings would still advance our understanding of sedation pharmacology in compromised airways. Either outcome will meaningfully inform clinical practice and future research directions in procedural sedation.

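### Propofol consumption is compared as unadjusted total milligrams although the first bolus is weight-based, so this secondary comparison loses precision, and its time window is unclear

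*Protocol article*

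**What the plan says.** In the protocol article, Outcomes and definitions {12} lists as a secondary outcome: "Total propofol dose defined as cumulative amount (mg, mean [SD]/median [IQR]) administered during procedure". The scale is raw milligrams. The same section times the length of the procedure from insertion of the gastroscope to its withdrawal.

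Intervention description {11a} sets the order of dosing. First: "An initial bolus of propofol (1.0–2.0 mg/kg for patients > 70 years; 1.5–2.5 mg/kg for patients < 70 years) injected". After that: "Then, esketamine 0.25 mg/kg is injected for the patients in Group E, while equal-volume saline solution is administered for Group C". Further boluses of 10–50 mg follow, titrated to effect. The maintenance rule begins "During the procedure, additional propofol (10–50 mg) could be administered again for maintaining a MOAA/S score of 2", then lists cough, grimacing and movement as further reasons, and ends with "hemodynamic instability (mean arterial pressure [MAP] increase" of at least 20 mmHg, or a heart rate rise of at least 20 beats/min.

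Background and rationale {6a} names "transient hypertension, tachycardia, and emergence phenomena" as possible side effects of esketamine at the studied dose and calls them typically mild and self-limited. The Discussion counts "propofol-sparing potential and hemodynamic stability" among the effects that the secondary outcomes should illuminate.

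Statistical methods {20a} compares continuous secondary outcomes by independent t-test or Mann–Whitney U test, two-sided at 0.05. Neither test takes account of weight.

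**The concern.** Three features of the definition weaken what this outcome can show.

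1. **Scale.** The initial bolus is proportional to body weight and is chosen within a range 1.0 mg/kg wide, before the study drug is given. Esketamine cannot reduce it. In raw mg with no adjustment, differences in weight and in that choice go straight into the standard deviation.

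2. **Window.** The words total and cumulative suggest that the initial bolus counts. But {11a} uses the procedure as the name for the phase after induction, and {12} times the procedure from scope insertion. On that narrower reading the initial bolus drops out, and so does the titration between study drug and insertion, where sparing could appear.

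3. **Meaning.** A rise in pressure or heart rate is an allowed reason for propofol and also an expected effect of esketamine. Some boluses in the esketamine group may follow the drug's own haemodynamic effect rather than light sedation.

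At stake is the reading of a secondary outcome that is meant to help explain any effect on hypoxemia. A real saving could be missed, or a small net saving misread as a small effect on sedative need.

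**Working it through.** The protocol states no effect size, SD or power for propofol dose, so there is no figure to reproduce. Everything below illustrates size on assumed inputs.

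**Inputs from the protocol.** Initial bolus 1.0–2.0 mg/kg (over 70 years) or 1.5–2.5 mg/kg (under 70); later boluses 10–50 mg; two-sided 0.05; 132 evaluable patients per group.

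**Assumed.** Mean weight W = 75 kg; weight SD s = 10 or 15 kg; initial dose uniform over its range, with mean m and variance v = 1/12; SD of the later boluses 25 or 40 mg, independent of weight and of the first bolus.

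**Step 1: spread of the initial bolus.** At 75 kg the range alone allows 75–150 mg or 112.5–187.5 mg. Variance = (W² + s²)(v + m²) − (Wm)².
- s = 15, m = 2.0: 5850 × 4.0833 − 22500 = 1387.5, SD 37.2 mg. Of this, m²s² = 900 (65%) is due to weight and (W² + s²)v = 487.5 to the choice of dose.
- s = 10, m = 1.5: 5725 × 2.3333 − 12656.25 = 702.1, SD 26.5 mg. Of this, 225 (32%) is due to weight and 477.1 to the choice of dose.

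**Step 2: detectable difference at 80% power.** This is (1.96 + 0.8416) × SD × √(2/132) = 0.3449 × SD. The SD of total mg is √(bolus variance + later variance). Weight adjustment removes the m²s² term.

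| Case | Later SD | Raw total: SD, difference | Weight-adjusted total: SD, difference |
|---|---|---|---|
| s = 10, 1.0–2.0 mg/kg | 25 | 36.4, 12.6 mg | 33.2, 11.4 mg |
| s = 10, 1.0–2.0 mg/kg | 40 | 48.0, 16.5 mg | 45.6, 15.7 mg |
| s = 15, 1.5–2.5 mg/kg | 25 | 44.9, 15.5 mg | 33.4, 11.5 mg |
| s = 15, 1.5–2.5 mg/kg | 40 | 54.7, 18.8 mg | 45.7, 15.8 mg |

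The gain runs from slight to substantial, depending mainly on the spread of weight. The expected between-group difference does not move, because the initial bolus precedes the study drug and is given blind.

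**Step 3: simulated power.** Assumed: 147 per arm, weight 78 ± 14 kg, initial dose uniform 1.5–2.5 mg/kg, later propofol with mean 60 mg, and a true 20% reduction in later propofol (12 mg).

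| Scenario | Total mg | Total mg/kg | Post-drug mg/kg |
|---|---|---|---|
| Later boluses scale with weight, SD 30 | 50% | 83% | 97% |
| Same, SD 40 | 47% | 71% | 86% |
| SD 30; top-ups offset 80–100% of a larger or smaller first bolus | 60–63% | 97–98% | 92–90% |

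If later boluses do not scale with weight (SD 30, no offset), total mg has about 65%. A separate set of simulations gave about 79–97% for total mg/kg or weight-adjusted total mg, against 50–75% for raw mg. Raw mg was lowest throughout. Whether post-drug mg/kg beats total mg/kg depends on how far top-ups compensate for the first bolus.

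**Step 4: the haemodynamic trigger.** Shift in the mean difference = (net extra share of esketamine patients triggered) × (bolus size). With assumed shares of 20–40% and a 30 mg bolus this is 6–12 mg, so a 20 mg saving in sedative need would appear as 14 to 8 mg. The shift is the same whether all propofol or only post-drug propofol is counted. The protocol gives no trigger frequency.

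**The case against.** The strongest reply is that nothing here is an error. Total propofol is a valid randomised comparison of net propofol use. A bolus given for a pressure rise is still propofol, with its respiratory effect, and belongs in a total. Leaving it out would select on clinicians' judgement after randomisation, where a pressure rise and light sedation overlap. All of that stands.

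It also rules out several stronger readings that a reader might infer:

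- **That the pre-drug bolus biases the result against esketamine.** It does not. It is given before the study drug by a blinded anaesthesiologist, so it only adds variance.
- **That most of the variable is pre-treatment noise.** With simulated SDs of about 36 mg for the initial bolus and 54 mg for the total, its share is 36²/54² = 1296/2916 = 44% of the variance.
- **That the outcome should be post-drug propofol alone.** Dosing is titrated to a sedation score, so a larger first dose may mean fewer top-ups, and the first dose is then part of the requirement. With full or near-full compensation, post-drug mg/kg has less power than total mg/kg. It also keeps every pressor-triggered bolus.
- **That pressor boluses could erase the sparing.** The trigger rates needed are guesses. The protocol calls these effects mild and says only that propofol could be given.
- **That the trigger and the listed side effects contradict each other.** They do not. Together they limit what the total means.

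It can also be said that weight adjustment belongs in an analysis plan and bolus reasons on a case report form. That is fair for details left open. But the article itself fixes raw mg and an unadjusted test, and its window can be read two ways.

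**Conclusion.** The point holds as a matter of precision and clarity in one secondary outcome. Raw mg without weight adjustment adds avoidable variance. In the analytic illustration the detectable difference is 12.6–18.8 mg instead of 11.4–15.8 mg, and in the simulations raw mg had the lowest power throughout. These figures rest on assumed weights, dose spread and sparing effect. That weight-driven variance is added follows from the weight-based bolus; the amount is uncertain.

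The window is ambiguous on the protocol's own wording. The total measures net propofol use, not sedative requirement alone, and the size of the gap between them cannot be known from the document. No bias in the comparison of net use is shown. The primary test and the sample size are not affected.

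**What to change.** - State the window: all propofol from the first bolus to scope removal.
- Analyse that total in mg/kg, or in mg with body weight as a covariate, and keep raw mg as a descriptive figure.
- As supporting analyses that do not replace the total, report propofol before and after the study drug separately. Where the reason for a bolus is recorded, also report post-drug propofol by reason.
- Interpret the total as net propofol use.

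The cost is a change of wording and slightly more analysis. Weight must already be known for dosing, and no extra patients or procedures are needed. Recruitment began in April 2025, so reasons may be missing for patients already enrolled, and the by-reason report should say for how many. This concerns measurement and analysis only; no dosing rule is proposed.

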## Statistical methods

### Statistical methods for primary and secondary outcomes {20a}

All analyses will be conducted using SPSS 23.0 (IBM Corp) by a statistician blinded to group allocation. The primary outcome will be analyzed using a one-sided *Z*-test at *α* = 0.025, while secondary outcomes will employ two-sided tests with *α* = 0.05.

Continuous variables will be assessed using the Kolmogorov–Smirnov test examining for normality. Normally distributed data will be presented as mean ± standard deviation (SD). Non-normal data will be presented as median or interquartile range (IQR). Categorical variables will be presented as counts and percentages.

For the primary outcome of hypoxemia incidence, we will employ a one-sided Z-test for proportions to evaluate the hypothesized reduction in the esketamine group, reporting absolute risk differences with 95% confidence intervals. Secondary outcomes will be analyzed using appropriate statistical tests based on variable characteristics: continuous normally distributed variables will be compared using independent *t*-tests, while non-normal continuous data will be assessed with Mann–Whitney *U* tests. Categorical outcomes will be analyzed using *χ*^2^ tests or Fisher’s exact tests as warranted by sample sizes. For time-to-event outcomes such as duration of hypoxemic episodes, we will utilize Kaplan–Meier survival analysis with log-rank tests. Longitudinal physiological measurements including mean arterial pressure and heart rate will be evaluated using repeated measures ANOVA, with post hoc Bonferroni corrections applied to account for multiple comparisons while maintaining the overall type I error rate at *α* = 0.05. All comparative analyses will be conducted by a blinded statistician using SPSS version 23.0, with two-sided tests (*α* = 0.05) employed for all secondary outcomes to conservatively assess potential group differences.

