### Adverse event reporting and harms {22}

All predefined sedation-related AEs (hypoxemia, hypotension) will be recorded in CRFs with severity grading (1–3), assessed for causality (Definite/Probable/Possible), and reported to IRB within 48 h (24 h for SAEs). Any participant experiencing trial-related adverse events/harms will receive immediate medical management, free follow-up care until resolution of symptoms, referral to appropriate specialists if needed, and some compensation according to hospital Compensation Policy.

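### Reflux and aspiration share one yes/no adverse-event item, so aspiration by arm cannot be derived from it, and its overlap with vomiting during the procedure is not settled

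*Protocol article*

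**What the plan says.** Under Outcomes and definitions {12}, the protocol article lists the adverse events to be captured on the case report form (CRF). The introduction to the list sets a general rule, "Occurrence counts and severity (where applicable) will be documented in the CRFs as follows", and a general window: "AEs will be documented and assessed continuously during the procedure and in the PACU".

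Two items matter here:

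- **Reflux and aspiration** are one item: "Reflux/aspiration: Defined as visible gastric content in the oropharynx or airway; recorded as presence/absence during the procedure". It is binary, has no grade, and covers the procedure only.
- **Nausea and vomiting** are a separate item: "Graded on a 3-point severity scale (1=mild/nausea only, 2=moderate/transient vomiting, 3=severe/prolonged vomiting"). It is "assessed both during the procedure and in the PACU".

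Adverse event reporting and harms {22} adds severity grading, causality assessment and expedited reporting ("reported to IRB within 48 h (24 h for SAEs")). It gives hypoxemia and hypotension as its examples and does not mention aspiration. Statistical methods {20a} compares categorical outcomes with χ² "tests or Fisher’s exact tests as warranted by sample sizes". It defines no total of adverse events and no any-event composite.

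**The concern.** The item joins two findings with an "or". Gastric contents in the oropharynx during upper endoscopy and gastric contents in the airway differ in clinical weight, yet either one alone satisfies the definition, and a yes/no entry does not show which was seen. This choice is made when the data are captured. An analysis plan cannot split the field afterwards without going back to source notes.

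The boundary with vomiting is also open. Vomited material visible in the oropharynx during the procedure literally meets the reflux/aspiration definition, and the same episode meets grade 2 or 3 of the nausea/vomiting scale. No rule assigns it to one item, to the other, or to both.

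What is at stake is how the safety result can be read. The trial is presented as evidence on sedation safety in patients at risk of obstructive sleep apnea. A difference in the merged rate could come from reflux, from aspiration, or from how vomiting was ticked. No difference in the merged rate would say little about aspiration.

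**Working it through.** The protocol states no rate for reflux, aspiration or vomiting, so there is no figure to reproduce. The check is a reading of the definitions, followed by an illustration under assumed rates.

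**Step 1: what each event produces on the form**

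| Event | Reflux/aspiration item | Nausea/vomiting item |
|---|---|---|
| Gastric contents in the oropharynx, no vomiting, during procedure | yes | not met by this finding |
| Gastric contents in the airway, no vomiting, during procedure | yes | not met by this finding |
| Vomiting during procedure, contents visible in the oropharynx | yes, on the literal wording | grade 2 or 3 |
| Vomiting in the PACU | no, outside the item's window | grade 2 or 3 |

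The first two rows are identical, so the predefined items cannot tell them apart. The third row meets both items. The fourth shows that the overlap is confined to the procedure.

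**Step 2: whether another section separates them**

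- The general rule in {12} allows severity where applicable, but this item is fixed as presence/absence.
- Sections {18a}, {5d} and {22} grade adverse events 1–3. A severity grade does not record where the contents were seen.
- Section {22} could produce a report of an individual serious aspiration. It defines no aspiration category to be assessed in every patient.

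**Step 3: how far merging dilutes a difference (assumed rates)**

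Let r be the reflux risk, equal in both arms, and a the aspiration risk, with the two independent. The risk on the merged item is then 1 − (1 − r)(1 − a).

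| Reflux r | Aspiration, control vs esketamine | Aspiration ratio | Merged item, control vs esketamine | Merged ratio |
|---|---|---|---|---|
| 5% | 0.5% vs 1.5% | 3.0 | 5.475% vs 6.425% | 1.17 |
| 5% | 1% vs 3% | 3.0 | 5.95% vs 7.85% | 1.32 |
| 10% | 0.5% vs 1.5% | 3.0 | 10.45% vs 11.35% | 1.09 |

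First row in full: 1 − 0.95 × 0.995 = 0.05475; 1 − 0.95 × 0.985 = 0.06425; 0.06425 / 0.05475 = 1.17. The absolute difference barely changes (0.95 instead of 1.0 percentage point). What is lost is the ratio and the ability to say which event caused the difference.

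**Step 4: what a separate field could and could not show**

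With the planned 147 per arm and a two-sided 0.05 Fisher's exact test, power for aspiration recorded alone is about 9% at 1% vs 3% and about 1% at 0.5% vs 1.5%. A separate field is therefore useful for description, not for testing. For example, 0 of 147 aspirations in an arm would give an exact 95% upper limit of 1 − 0.025^(1/147) = 2.5%. The merged item cannot supply that statement about aspiration unless nobody in the arm has reflux either.

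**The case against.** The strongest reply is that aspiration would not disappear. Section {5d} requires all adverse events to be reported with grades, {18a} has them graded by blinded assessors, and {22} sets a 24-hour route for serious events. A clinically serious aspiration would probably leave its own record, and that record could be tabulated by arm. The CRF is also not shown, and an article condenses the full protocol, so sub-fields may exist.

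Part of this stands. A reader might infer that the trial cannot report aspiration at all, and the documents do not support that; the limit is on what the predefined item yields. But event reports are not a defined outcome assessed in the same way in every patient. The article also does more than omit a detail: it states the definition and the recording scale, and both merge the two events.

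A reader might also infer that a vomiting patient is counted twice. The documents do not support this either. The items are reported separately, no sum or composite is planned, and a patient who appears under two adverse-event terms is ordinary safety reporting. What remains is narrower: for vomiting during the procedure, no rule says which item applies.

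Finally, one might argue that separating the events would give the trial useful power for aspiration. That would take a large rise in a rare event, for which the documents give no basis. At more modest differences, power is low however the item is recorded.

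**Conclusion.** The point holds in a limited form and is minor. As written, the item cannot separate aspiration from reflux, no other section defines aspiration as a systematic per-arm outcome, and the classification of intra-procedural vomiting is undefined. These conclusions rest on the wording of {12} and need no assumed rate. The size of the dilution does rest on assumptions: reflux equal in both arms, independence of the two events, and illustrative rates that the protocol does not give. In the three scenarios shown, a threefold aspiration ratio becomes 1.09 to 1.32. The primary outcome, sample size and randomization are not affected.

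**What to change.** Replace the single item with two yes/no CRF fields:

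1. Reflux: gastric contents seen in the oropharynx.
2. Aspiration: gastric contents seen in the airway.

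Add one sentence on how vomiting during the procedure is classified: under nausea/vomiting only, or under both items. Report each field descriptively by arm as count, percentage and exact 95% confidence interval.

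The cost is one extra CRF field. According to the Trial status section, enrolment began on April 1, 2025, so patients already entered need a source-note check to recode the merged item. Some notes may not say where the contents were seen. Those patients should be reported as unclassified rather than assigned to either field. The recoding should be done by staff blinded to allocation.

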## Discussion

This single-center, prospective, randomized controlled trial rigorously investigates the potential of low-dose esketamine (0.25 mg/kg) to mitigate propofol-induced hypoxemia in moderate-to-high risk OSA patients undergoing painless gastroscopy. Our study design addresses critical gaps in current sedation practices for this vulnerable population (patients with moderate-to-high risk OSA) by systematically evaluating whether low-dose esketamine reduces hypoxemia incidence while maintaining hemodynamic stability during procedural sedation.

The high incidence of hypoxemia (26–85%) during propofol sedation in OSA patients arises from multifactorial pathophysiology [19–21], including anatomical airway obstruction, sedative-induced respiratory depression, chronic pharyngitis, lung compression, and procedural factors. While airway optimization remains fundamental, our focus on pharmacological adjuvants represents a novel approach to this persistent clinical challenge. The selection of esketamine is particularly promising given its unique pharmacodynamic profile that may counteract propofol’s respiratory depressive effects while maintaining adequate sedation [14, 15].

Several methodological strengths enhance the validity of our trial design. First, our use of STOP-Bang scoring (≥ 3) provides a validated, clinically practical method for OSA risk stratification [22, 23], with clear correlation to polysomnography-confirmed disease severity. Second, we have implemented objective, clinically relevant endpoints aligned with international sedation guidelines [24], including both incidence and duration metrics for hypoxemia. Third, our protocol incorporates robust safety measures, including strict gastroscopy procedure time limits (≤ 15 min) based on our previous findings [25] and comprehensive monitoring of laryngospasm as a potential indicator of esketamine’s airway protective effects.

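### Laryngospasm and reflux/aspiration are recorded only during the procedure, and mask ventilation counts only if it interrupts the procedure, although the stated windows for these items include the PACU

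*Protocol article*

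**What the plan says.** All the definitions are in the protocol article, Outcomes and definitions {12}.

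- The sentence that introduces the adverse event list sets one window for all of it: "AEs will be documented and assessed continuously during the procedure and in the PACU". The items that follow are presented as the way events go onto the CRF.
- Three items keep to that window. Cough is "Defined as ≥2 consecutive coughs during the procedure or in the PACU", hiccups are "recorded as presence/absence during the procedure or in the PACU", and nausea/vomiting is "assessed both during the procedure and in the PACU".
- Two items do not. Reflux/aspiration is "Defined as visible gastric content in the oropharynx or airway; recorded as presence/absence during the procedure". Laryngospasm is "assessed by auscultation and waveform capnography, and recorded as presence/absence during the procedure".
- Emergency airway intervention, a secondary outcome, consists of jaw thrust and then "mask-assisted ventilation with procedure interruption, tracheal intubation during procedure and in PACU".

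The Discussion lists among the trial's safety measures "comprehensive monitoring of laryngospasm as a potential indicator of" airway protection by esketamine.

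**The concern.** The introductory sentence and two of the items beneath it give different windows for the same events. Because the PACU is named for the three milder items, anyone completing the CRF could reasonably take its absence from laryngospasm and reflux/aspiration as intended. The mask-ventilation wording has a related fault: the outcome's window includes recovery, but the qualifier attached to this component cannot be met there.

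Recovery matters for these items. Under Provisions for post-trial care {30}, patients go to the PACU once they can breathe spontaneously. Recovery time is measured from scope removal to an MOAA/S score of 5 or response to normal voice, so a patient may still be sedated on arrival. If PACU events are scored absent, the comparison of arms on these airway harms describes the procedure alone. The Discussion's description of laryngospasm monitoring as comprehensive would then not match the item.

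**Working it through.** The plan gives no figure on this point, so there is none to reproduce. The check compares the stated windows.

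**Step 1. What counts as the procedure.** The section measures procedure length from insertion of the gastroscope to its complete withdrawal, and recovery time from scope removal. A window limited to the procedure therefore does not naturally extend to the PACU.

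**Step 2. Listed adverse event items against the introductory window (procedure and PACU).**

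| Item | Procedure | PACU | Agrees with introductory sentence |
|---|---|---|---|
| Cough | yes | yes | yes |
| Hiccups | yes | yes | yes |
| Nausea/vomiting | yes | yes | yes |
| Reflux/aspiration | yes | no | no |
| Laryngospasm | yes | no | no |

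Three of 5 items agree and 2 of 5 do not.

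**Step 3. Components of emergency airway intervention (stated window: procedure and PACU).**

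| Component | Can be met in the procedure | Can be met in the PACU |
|---|---|---|
| Jaw thrust | yes | yes |
| Mask-assisted ventilation | yes, if the procedure is interrupted | no, as there is no procedure left to interrupt |
| Tracheal intubation | yes | yes |

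Two of 3 components can be met in the PACU and 1 of 3 cannot.

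**Step 4. Does other text widen the definitions?**

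- Trial design {8}: vital signs are monitored through PACU recovery.
- Provisions for post-trial care {30}: supportive treatment after scope removal is recorded on CRFs and reported to the IRB.
- Plans for assessment and collection of outcomes {18a}: graded adverse events are also collected after the procedure.
- Composition of the coordinating center and trial steering committee {5d}: reporting of all adverse events is mandatory.
- Adverse event reporting and harms {22}: reports go to the IRB within 48 h, or 24 h if serious, with no limit to the procedure.

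These provisions govern monitoring, capture and reporting. None redefines the laryngospasm, reflux/aspiration or mask-ventilation item. A laryngospasm in the PACU could be reported to the IRB and still be scored absent on the trial's laryngospasm item.

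**The case against.** The strongest reply is that nothing is lost. The general provisions in step 4 above would capture a serious airway event in recovery, and jaw thrust or intubation in the PACU counts under emergency airway intervention. This stands. A reader might infer that serious airway events in recovery disappear from the trial, or that a patient mask-ventilated for laryngospasm in the PACU is negative on every airway item. The documents support neither inference. The events have reporting routes, and such a patient is positive on emergency airway intervention if jaw thrust or intubation was also used.

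A second reply is that the introductory sentence governs the list and the narrower wording is loose drafting. That is possible. Neither the assessment schedule (Fig. 3) nor the CRF is shown, and either might state the windows. But the printed text supports both readings, and the more specific wording is the narrower one. A clear schedule would still leave this section in conflict with itself.

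A third reply is that the Discussion calls laryngospasm only a potential indicator and rests no conclusion on it. That is fair. The mismatch is with the word comprehensive, not with any claimed result.

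Finally, waveform capnography is named for the gastroscopy room (Intervention description {11a}), while only vital signs are named for the PACU. Laryngospasm may therefore be harder to confirm there by the stated method. That limits how it can be assessed in the PACU, and the fix should allow for it. It does not remove the conflict between the windows.

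**Conclusion.** The inconsistency is real but limited. Two of the 5 listed adverse event items contradict the window set by the sentence that introduces them, and 1 of the 3 airway-intervention components cannot be met in part of its own window. If the items are scored as written, the predefined between-arm counts of laryngospasm, reflux/aspiration and mask ventilation would miss recovery.

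This rests on two assumptions: that the item wording, not the introductory sentence, determines the CRF entry, and that the stated PACU window belongs to emergency airway intervention as a whole and not only to intubation. Under the narrower reading of that window, mask ventilation would still not count in the PACU, and the definition would need clarifying in any case.

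The effect on event counts cannot be put in numbers, because the documents give no PACU event rate, PACU length of stay or expected difference between arms. A bias favouring either arm is possible but not shown. The primary outcome and the sample size are untouched. The passages should be reconciled, as they bear on the airway-safety comparison.

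**What to change.** In Outcomes and definitions {12}:

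1. Give laryngospasm and reflux/aspiration the window already set by the introductory sentence, procedure and PACU, with presence or absence recorded separately for each phase. State that laryngospasm in the PACU is assessed by the monitoring available there.
2. Define the mask-ventilation component by phase: with interruption of the procedure while it is under way, and any mask-assisted ventilation in the PACU.
3. Report each of these items by phase and in total, by arm.

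Trial status describes the trial as ongoing, with recruitment planned to December 31, 2026. The change should be made without sight of results by arm, and Fig. 3 and the CRF checked for agreement.

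The cost is modest: outcome wording and a few CRF fields, with no added visit, since adverse events are already collected after the procedure. Reported counts may rise slightly, and PACU laryngospasm may have less capnographic confirmation than events during the procedure. Reporting by phase keeps that difference visible. For patients already treated, PACU status would have to come from the adverse event records already held.
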